#### Cost-related data

The feasibility of collecting direct and indirect cost data will be assessed. Participants will be asked to report their current medication use, including over-the-counter medication (type, dose, frequency) for management of WAD. They will also be asked to retrospectively report their daily medication use and health service use, including medical (including radiology/imaging), allied health and complementary (eg, massage, acupuncture) over the past week. Participants will also be asked to report their pre-injury and current work status, gross yearly salary range and percentage of regular work capacity, insurance claim status, any legal involvement and any finalised claim payout amounts. These data will be used to inform the design of a future within-trial full economic evaluation. The costs of delivering the intervention (eg, SMS messages, clinician time) will also be estimated.

#### Acceptability

An adapted version of the Technology Acceptance Model (TAM)^29^ will be used to assess perceived ease of use and perceived usefulness of the RISE intervention. Each construct is measured using six items rated on a 7-point scale from 1 (‘Strongly disagree’) to 7 (‘Strongly agree’). Mean scores will be calculated for each subscale, and participants will be classified as meeting the acceptability criterion if both subscale mean scores are≥4.0. TAM items will be framed in the future tense at baseline to assess anticipated acceptability and in the past tense at follow-up to assess experienced acceptability following intervention use.^30^

Additional indicators of acceptability will include responses to purpose-built items, including participant intention to use (or continue using) the intervention, willingness to recommend the intervention to others with WAD and Session Rating Scale scores for participants who complete the clinician-guided session/s.^31^ Intervention-specific items assessing perceived informational support, emotional support, encouragement for behaviour change and confidence in managing recovery will also be included. These items were developed to align with the core domains of the RISE intervention. In addition, behavioural indicators of acceptability will be examined and summarised. These include participant engagement with optional or self-initiated features, such as use of the on-demand message function, ‘snooze’ or ‘stop’ functions and weekly diaries, as well as the frequency of use of these features. Participant feedback on message frequency and perceived helpfulness will also be assessed. These behavioural indicators provide additional insight into patterns of participant engagement beyond the core intervention components. Finally, we will examine time participants wear the device, including the extent of valid data derived from the wearable device.

Patient experience and clinician and funder perspectives, including those of CTP insurance representatives, will be explored as part of the process evaluation. Individual semi-structured interviews and focus groups will examine the perceived value and implementation potential of the RISE intervention as well as opportunities for optimisation. Sessions will be co-facilitated by research staff experienced in co-design and qualitative methods, audio-recorded and transcribed verbatim.

#### Assessment of participant blinding

To assess the success of participant blinding, participants will be asked at the post-intervention follow-up which study group they believe they were assigned to (RISE intervention, active control or unsure). Participants will also rate their confidence in this belief on an 11-point scale (0=not at all confident to 10=extremely confident) and will be invited to provide a brief explanation for their response. Responses will be summarised descriptively to assess the extent to which participants were able to correctly identify their allocation. This information will be used to evaluate the feasibility of maintaining participant blinding in a future definitive trial.

### Health outcomes and screening measures

During the baseline survey, participants will be asked a range of demographic and clinical and health-related questions. Demographic questions include age, gender and socioeconomic information (education, employment, marital status, language and English proficiency, postcode). Clinical, health and technology information will include time since the RTI, current diagnoses and digital and SMS literacy.

#### Risk of poor recovery

Participants will complete the WhipPredict as a screening measure only. Participants are asked to indicate how their neck pain has affected their ability to manage in everyday life, such as pain intensity, personal care, lifting, reading, headache, concentration, work, driving, sleep and recreation. Responses are on a scale of 0–5, with each point indicating how much that item affects them in their everyday life. If a participant is over the age of 35, they are asked to complete five more questions relating to hyper-arousal symptoms. Items are rated on a 4-point scale, ranging from ‘not at all or only one time’ to ‘5 or more times a week/almost always’. The total score obtained indicates the level of risk which is used to predict outcomes such as the likelihood of developing moderate/severe disability or experiencing full recovery from acute whiplash injury.^32^ It demonstrates good prognostic accuracy (area under the curve (AUC) ≈0.73–0.80) for identifying individuals at risk of poor recovery.^32^

#### Psychological distress

Non-specific psychological distress will be assessed using the K6.^23^ It is used during screening to determine the presence of acute psychological distress that would preclude involvement in the study and will be repeated at follow-up time points. Items are measured on a 5-point Likert scale, ranging from 1 (‘All of the time’) to 5 (‘None of the time’) and ask participants to indicate how they have been feeling during the past 30 days (eg, how… nervous, hopeless, restless/fidgety, worthless, that everything was an effort).

The Credibility/Expectancy Questionnaire^33^ assessed at baseline will measure how much participants believe that the intervention will help to improve their recovery. The measure is based around two key aspects of *belief:* (1) what one *thinks* will happen and (2) what one *feels* will happen. Participants will answer 2 sets of questions. Set 1 comprises four questions, three of which are scored on a 9-point scale ranging from 1 (‘Not at all logical’) to 9 (‘Very logical’). Questions include, “At this point, how successfully do you think this intervention will be in reducing your [pain/stress] symptoms?” The last question in Set 1 asks, “By the end of the intervention period, how much improvement in your pain/stress symptoms do you think will occur?” and is answered as a percentage, ranging from 0 to 100%. Set 2 comprises two questions about how participants feel about the intervention and its likely success answered on the same 9-point scale.

#### Pain and disability

The experience of pain will be measured at baseline and at all follow-ups using the Brief Pain Inventory.^34^ Participants rate pain severity by reporting their worst, least, average and current pain over the past 24 hours using 11-point numerical rating scales ranging from 0 (‘No pain at all’) to 10 (‘Pain as bad as you can imagine’). Participants report current pain management strategies and the percentage of pain relief obtained from treatments or medications over the past 24 hours.

Pain tolerability and comfort will be measured at baseline and all follow-ups using single items. Participants rate pain intensity ‘over the past 24 hours’ and ‘right now’ on a scale of 0 (‘No pain’) to 10 (‘Pain as bad as you can imagine’) and their pain tolerability ‘over the past 24 hours’ and ‘right now’ on a scale of 0 (‘Completely tolerable’) to 10 (‘Completely intolerable’); these items are adapted from Markman *et al*.^35^

Using a purpose-built measure, participants rate their level of comfort by reporting their comfort at its worst, at its least, on average and right now on a scale of 0 (‘Not comfortable at all/No comfort’) and 10 (‘The most comfortable I have ever been/High comfort’). Participants also report their level of discomfort on a scale of 0 (‘No discomfort at all/No discomfort’) and 10 (‘The most uncomfortable I have ever been/High discomfort’).

Pain-related disability will be measured at baseline and at all follow-ups using the Neck Disability Index.^36^ Participants are asked to indicate how their neck pain has affected their ability to manage in everyday life, with items related to pain intensity, personal care, lifting, reading, headache, concentration, work, driving, sleep and recreation. Participants answer each item on a scale of 0–5, with each point indicating how much that item affects them in their everyday life.

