**Assessments**						
Expectancy and acceptability						
Credibility/Expectancy Questionnaire		X				
Acceptability (Technology Acceptance Questionnaire and purpose-built items)		X			X	X
Session Rating Scale (RISE only)				X		
Blinding assessment (perceived group allocation)					X	
Pain and disability						
Pain tolerability and comfort		X			X	X
Pain intensity (Brief Pain Inventory)		X			X	X
Neck Disability Index (NDI)		X			X	X
Psychological						
DASS-21		X			X	X
Post-Traumatic Stress Disorder single items*		X			X	X
Primary care PTSD screen		X			X	X
PCL-5 (only if PTSD screening is positive)		X			X	X
Quality of life and well-being						
EQ-5D-5L		X			X	X
Global Impression of Change					X	X
Cost-related						
Health service and medication use		X			X	X
Compensation claim and lawyer involvement		X			X	X
Work/income status		X			X	X

* These items guide the tailoring of the messages.

DASS-21, 21-item Depression Anxiety and Stress Scale; EQ-5D, EuroQol-5 Dimension (health-related quality of life); GIC, Global Impression of Change; PCL-5, PTSD Checklist for DSM-5 ; PTSD, Post-Traumatic Stress Disorder; RISE, recovery, information, support and empowerment; SMS, short message service; SPIRIT, Standard Protocol Items: Recommendations for Interventional Trials.

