### Data analysis

Participant characteristics and baseline measures will be summarised using descriptive statistics. As this is a feasibility trial, analyses will be primarily descriptive and will focus on estimating feasibility parameters. Feasibility outcomes (recruitment, retention, intervention engagement, data completeness and acceptability) will be descriptively summarised. These estimates will be interpreted against the pre-defined progression criteria (see table 2) together with the process evaluation data to determine whether a future definitive trial is warranted. Final progression decisions will be made by the Trial Management Committee based on the overall pattern of feasibility findings across domains, together with qualitative process data and consideration of whether any identified barriers are modifiable. Where findings are mixed, decisions regarding progression will consider the pattern of results across domains, the nature and modifiability of barriers and the potential for refinements prior to a future trial. Participant responses regarding treatment allocation will also be summarised descriptively and compared with actual allocation to assess the success of participant blinding. No formal imputation of missing data is planned. The extent and patterns of missing data will be examined as part of the feasibility evaluation of the data collection procedures.

Preliminary changes in patient-reported outcomes will be explored using estimates of between-group differences with 95% CIs at each follow-up time point. These analyses will be conducted on an intention-to-treat basis. As this feasibility study is not powered to evaluate clinical effectiveness, no formal hypothesis testing will be undertaken and estimates will be interpreted cautiously with consideration of the width of the CIs. These exploratory analyses are intended to identify preliminary signals of potential clinical benefit, assess the suitability and responsiveness of candidate outcomes and inform the selection of the primary clinical outcome for a future definitive trial.

Qualitative interview and focus group data will be analysed using reflexive thematic analysis^44

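### As described, the purpose-built comfort measure asks for the lowest comfort twice and never for the highest (minor; check the item wording)

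*Protocol article*

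**What the plan says.** The Pain and disability section of the protocol article describes two sets of ratings with nearly the same four labels.

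- **Pain (Brief Pain Inventory):** "Participants rate pain severity by reporting their worst, least, average and current pain over the past 24 hours". The anchors put no pain at 0 and the worst imaginable pain at 10, so higher is worse.
- **Comfort (purpose-built):** "participants rate their level of comfort by reporting their comfort at its worst, at its least, on average and right now". The anchors put absence of comfort at 0 and the greatest comfort ever felt at 10, so higher is better.

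The comfort ratings are followed by a separate rating: "Participants also report their level of discomfort on a scale of 0 (‘No discomfort at all/No discomfort", with high discomfort at 10. On timing the section says "Pain tolerability and comfort will be measured at baseline and all follow-ups using single items". Table 1 lists "Pain tolerability and comfort" at baseline, week 6 and 3 months.

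The Data analysis section says the exploratory comparisons of patient-reported outcomes are meant, among other things, to "assess the suitability and responsiveness of candidate outcomes and inform the selection of the primary clinical outcome for a future definitive trial".

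**The concern.** The pair *worst* and *least* brackets a scale only when a high score is bad. On a comfort scale, where a high score is good, the two labels fall at the same end. Followed as described, the measure asks for the low extreme twice and leaves the high extreme unasked.

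What is at stake is the usefulness of the comfort data for one stated purpose. The trial intends to judge how suitable and responsive its candidate outcomes are. A new, purpose-built measure is what a feasibility trial should test cleanly. If one of its four ratings is redundant or ambiguous, that rating says little about the construct, and no analysis can later recover a highest-comfort value that was never requested.

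**Working it through.** No sample size, power or error rate is involved, and the article gives no figure to reproduce. The check is to map each label to the point of the scale it asks for, using the anchors in the Pain and disability section.

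| Label | Pain (0 = none, 10 = as bad as imaginable) | Comfort (0 = none, 10 = most comfortable) |
|---|---|---|
| Worst | highest score | lowest score |
| Least | lowest score | lowest score |
| Average | typical score | typical score |
| Current / right now | present score | present score |

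1. **Pain.** *Worst* and *least* are the maximum and minimum. Together they bracket the range.
2. **Comfort.** Comfort is at its worst when there is least of it. *Worst* and *least* are therefore both the minimum, and no label asks for the maximum.
3. **Can another comfort rating supply the maximum?** No. An average and a present value do not give the peak.
4. **Can the discomfort rating supply it?** No. It is a separate scale with its own anchors, and the article describes no best, worst or least version of it.
5. **Does another section correct it?** No. Table 1 gives only the name of the measure and its timing, and the Data analysis section does not describe its items.
6. **Likely origin.** The four labels are those of the Brief Pain Inventory ratings earlier in the same section, applied to a scale that runs the other way. This is an inference from the matching labels; the article does not say so.

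**The case against.** The strongest reply is that the questionnaire is not shown. The response anchors are given in quotation marks, but the four labels are not, so they read as the article's paraphrase. The REDCap item may already ask for comfort at its best, with the slip made only when the article was written. This stands. A reader might infer that best comfort is certainly never measured; the article supports that only for the measure as described.

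A reader might also try to put a size on the problem. Take invented ratings with lowest comfort 2, highest 8, average 5 and current 5. The mean as written is (2 + 2 + 5 + 5)/4 = 3.5, against (2 + 8 + 5 + 5)/4 = 5.0 with a highest-comfort item. The arithmetic is right, but the article defines no comfort mean or total and introduces the measure as single items. If the ratings are reported one by one, no such shift arises, and *average* and *right now* are untouched.

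Nor does the article show that respondents would take *least* to mean least discomfort and answer at the opposite end. The explicit anchors and the separate discomfort scale make that less likely, though they do not exclude it. If it did happen, it would be a further measurement problem and not a rescue.

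Finally, it may be said that the trial would find the flaw itself, since two near-identical ratings should stand out when candidate outcomes are assessed. That is fair against any claim that the flaw will pass into the definitive trial. It is no reason to leave the wording alone now, because the missing rating still could not be recovered.

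**Conclusion.** The point holds on the text as written: two of the four comfort ratings ask for the lowest comfort, and none asks for the highest. Nothing else in the article repairs this.

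Its size is small. Comfort is one of several exploratory outcomes, alongside pain, disability, psychological symptoms and quality of life. It is not among the progression criteria in Table 2, no sample size depends on it, and no formal hypothesis testing is planned. Both groups are scheduled for the same measure, so the wording gives no ground for claiming a between-group bias. No numerical effect can be stated.

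The conclusion rests on one assumption, that the article reports the item labels faithfully. If it does not, only the article's text is at fault.

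**What to change.** - **Check first.** Compare the REDCap wording of the four comfort ratings with the article.
- **If the item matches the article,** reword the *least* rating to ask for comfort at its best (most comfortable). Keep the other three ratings and the 0–10 scale, and use the same wording at baseline, 6 weeks and 3 months.
- **If the item is already correct,** correct the sentence in the article.
- **If data have already been collected with the flawed wording,** do not interpret the *least* rating as the upper extreme. Rely on the *average* and *right now* ratings when judging comfort as a candidate outcome.

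The cost is one reworded item and, at most, a minor ethics notification. The measure is purpose-built, so no validated instrument is altered.

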#### Depression, anxiety and stress

Depression, anxiety and stress symptoms will be measured at baseline and at all follow-ups using the 21-item Depression Anxiety and Stress Scale (DASS-21).^37^ Participants will be asked to read each statement and indicate how much the statement has applied to them over the past week, from ‘0 – Did not apply to me’ to ‘3 – Applied to me very much or most of the time.’ Example statements include, ‘I found it hard to wind down’.

#### Post-traumatic stress symptoms (PTSD)

Post-traumatic stress symptoms will be assessed at baseline and at all follow-ups using a two-stage approach. Participants will first complete the Primary Care PTSD Screen for DSM-5 (PC-PTSD-5),^38^ a 5-item screening measure designed to identify probable PTSD symptoms experienced over the past month. Participants respond ‘Yes’ or ‘No’ to items assessing re-experiencing (eg, unwanted memories or nightmares), avoidance of trauma-related thoughts or reminders, hyperarousal (eg, being on guard or easily startled), emotional numbing or detachment and trauma-related guilt or self-blame. Participants scoring ≥3 on the PC-PTSD-5 will subsequently complete the PTSD Checklist for DSM-5 to assess the severity of PTSD symptoms. The PCL-5^39^ is a 20-item self-report measure assessing DSM-5 PTSD symptom clusters over the past month, with higher scores indicating greater symptom severity.

Additionally, three items adapted from Horwitz^40^ will be used to inform real-time tailoring of the SMS messages. Participants will rate the extent to which they currently feel nervous, worried or anxious they are and the extent to which they are re-hashing the circumstances related to the car accident on a 5-point scale (‘Not at all’ to ‘Extremely’). Participants will also report on their current problems with fatigue on an 11-point scale, with 0 being ‘No problem’ and 10 being ‘Severe problem’.

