### Intervention condition: RISE

The RISE intervention is a tailored text message-based intervention to support the recovery journey for patients with acute WAD from an RTI. It is delivered over a 3–4 week period, where messages will be sent to patients targeting two treatment mechanisms identified in prior research: stress symptom management and improved pain coping skills^14^ in addition to recommended exercise and activity. Message content was further developed in line with themes identified from prior work co-designing the intervention (*manuscript under review*). These themes included: 1) What can I expect in terms of RTI symptoms and the recovery process? 2) What can I do to help myself? and 3) What are these unexpected emotions and trauma responses, and are they normal? The timing, intensity and frequency of the messages will be tailored to patient preferences where possible. RISE includes four core domains, which underpin the content of the messages, as outlined:

**R**ecovery-focused messages that provide reassurance, encouragement and emotional support.**I**nformational support providing education on whiplash injury and pain and what to expect during recovery.**S**upport for behaviour change, including psychological techniques.**E**mpowering and motivational messages to enhance patient confidence in managing their pain and recovery.

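### A follow-up PCL-5 difference between arms would compare subsets selected by a post-randomisation screen, because the general analysis rule makes no exception for this gated scale

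*Protocol article*

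**What the plan says.** Under Post-traumatic stress symptoms (PTSD), the protocol article sets the timing, "Post-traumatic stress symptoms will be assessed at baseline and at all follow-ups using a two-stage approach", and the gate, "Participants scoring ≥3 on the PC-PTSD-5 will subsequently complete the PTSD Checklist for DSM-5 to assess the severity of PTSD symptoms". The Psychological block of Table 1 agrees. The screen is marked for everyone at baseline, week 6 and 3 months. The PCL-5 is marked at the same three points with the condition "PCL-5 (only if PTSD screening is positive".

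Data analysis gives one rule for all such measures: "Preliminary changes in patient-reported outcomes will be explored using estimates of between-group differences with 95% CIs at each follow-up time point". It adds "These analyses will be conducted on an intention-to-treat basis" and "No formal imputation of missing data is planned". One stated use of these estimates is to "inform the selection of the primary clinical outcome for a future definitive trial"; the others are to look for signals of benefit and to judge how responsive the candidate outcomes are. The PCL-5 is neither named nor excepted, and nothing is said about participants who screen negative.

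Under Intervention condition: RISE, the two targeted mechanisms are "stress symptom management and improved pain coping skills".

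**The concern.** Gating at baseline does no harm to the comparison, because the baseline survey precedes randomisation. Gating at 6 weeks and 3 months is different. Whether a participant has a follow-up PCL-5 score then depends on the screen result at that assessment, which comes after allocation and can be altered by it. A participant who improves to below 3 on the screen leaves the PCL-5 data, and one who worsens enters it. If RISE shifts symptoms, the two arms' scored subsets are no longer comparable, although the plan labels the analysis intention-to-treat.

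Change from baseline also has a gap. Someone positive at baseline and negative later has no follow-up score, and someone negative at baseline and positive later has no baseline score. These are the people whose change says most about responsiveness.

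At stake is the PCL-5's standing as a candidate outcome. It is the 20-item severity measure for trauma symptoms in the schedule, and the estimates are meant to guide the choice of primary outcome for the definitive trial. The advice to interpret with regard to CI width does not help here, because the width reflects imprecision and not selection.

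**Working it through.** The plan gives no PCL-5 mean, SD, effect size or screen-positive rate, so there is no figure of its own to reproduce. The inputs from the document are 25 per arm (RCT sample size), the cut of 3 on the screen, and 70% as the green retention threshold (Table 2). Everything else below is assumed and only shows what gating can do.

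**Assumptions, first set.** Follow-up PCL-5 in controls S ~ N(30, 15²). Screen positive if S + noise > 33, with noise ~ N(0, 7²). The same screen acts on the RISE scores after the benefit is applied.

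**Uniform benefit of 7.5 points, closed form.**
- SD of the screen variable = √(15² + 7²) = √274 = 16.55.
- For an arm with mean m: a = (33 − m)/16.55; share positive = 1 − Φ(a); mean PCL-5 among positives = m + (225/16.55) × φ(a)/(1 − Φ(a)).
- Control, m = 30: a = 0.181, share 43%, mean = 30 + 13.59 × 0.917 = 42.46.
- RISE, m = 22.5: a = 0.634, share 26%, mean = 22.5 + 13.59 × 1.241 = 39.37.
- Gated difference = 39.37 − 42.46 = −3.1 against a true −7.5. The loss is 1 − 3.1/7.5, about 59%.

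**Other shapes of benefit, by simulation** (400,000 per arm). The full difference has a simple form in each case.

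| Who benefits | Full difference | Gated difference |
|---|---|---|
| Nobody | 0 | about 0 |
| Everyone, 7.5 points | −7.5 | −3.1 |
| Proportional, 25% (0.25 × 30) | −7.5 | −6.9 |
| Only S < 40, 10 points (10 × Φ(0.667) = 10 × 0.75) | −7.5 | +3.7 |
| Only S > 40, 10 points (10 × 0.25) | −2.5 | −5.3 |
| Excess above 30 halved (½ × 15 × 0.399) | −3.0 | −6.4 |

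Simulated entries move by about 0.1 between runs. A run of 4,000,000 per arm gave −7.0 and −5.2 where the table has −6.9 and −5.3. The rows show dilution, near-agreement, reversal and exaggeration.

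**Second set of assumptions.** Control mean 25, SD 16; correlation of screen with PCL-5 from 0.6 to 0.9; control screen-positive share 30%, 50% or 70%.
- A uniform −8 becomes −3.1 to −6.5, and a uniform −4 becomes −1.6 to −3.3.
- With a 10-point benefit confined to milder cases (correlation 0.8), the full difference is about −7.7. The gated difference is +3.0, +0.8 or −1.9 at control shares of 30%, 50% and 70%, so reversal is possible but not assured even for this shape.

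**Numbers with a score.** At 70% retention, 25 × 0.70 = 17.5 per arm.
- Under the first set with uniform benefit: 17.5 × 0.43 = 7.5 controls and 17.5 × 0.26 = 4.6 RISE participants.
- 95% CI half-width in SD units of the scored subset: 1.96 × √(1/7.5 + 1/4.6) = 1.16.
- If everyone retained were scored: 1.96 × √(2/17.5) = 0.66.
- With equal screen-positive shares of 20% to 70% in both arms, 3.5 to 12.2 per arm would be scored, with half-widths of 1.48 to 0.79.

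**The case against.** The strongest reply is that Data analysis never names the PCL-5. The scale's stated job is to grade severity in people who screen positive, which is a sound use of two-stage screening, and how a conditionally given scale is analysed may be settled in an analysis plan not shown. Part of this stands: no sentence commits to a PCL-5 contrast, and the conflict arises by default from a general rule. But the rule covers patient-reported outcomes without exception, and no later plan can recover scores that were never collected.

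A second reply is that little depends on it. The trial is a feasibility study with no hypothesis tests, no criterion in Table 2 uses a clinical score, and about 7 against 5 scores would give an interval too wide to read as a signal. This stands as a limit on severity.

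A third is that other measures cover the targeted construct. The DASS-21, the PC-PTSD-5 and the three tailoring items go to everyone at all three assessments, so randomised comparisons of stress and of the screen score remain available. This also stands.

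A reader might infer that gating always pulls the estimate toward no effect or the wrong sign. The table above contradicts that: a benefit concentrated in severe cases is exaggerated, and a proportional one is almost unchanged. Reversal needs a benefit confined to milder cases, for which the document offers no evidence.

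**Conclusion.** The point holds in limited form. As written, the plan yields a follow-up PCL-5 difference between subsets defined by a post-randomisation screen. That is not a randomised comparison and does not fit the stated intention-to-treat basis. This conclusion needs no assumed number. It rests on reading the two-stage procedure as applying afresh at each assessment, which is the natural reading of the text and Table 1, and on the PCL-5 counting as a patient-reported outcome.

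The size and direction of the bias cannot be known from the document. Under the illustrative inputs, a true −7.5 may appear as anything from about −6.9 through −3.1 to +3.7, and a true −2.5 may appear as about −5.3. If RISE has no effect on symptoms, there is no bias.

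The document does not support reading this as a threat to the feasibility conclusions, or as leaving stress and PTSD symptoms without any valid comparison. The harm is confined to using the PCL-5 as a signal of benefit or as a candidate outcome. It should be fixed, but it is not a blocking fault.

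**What to change.** In Data analysis, add a sentence that the between-group PTSD outcome at 6 weeks and 3 months is the PC-PTSD-5 total (five yes/no items, 0–5), collected from all participants. State also that PCL-5 scores are reported descriptively by arm, with the number screening positive at each assessment and no between-group estimate. This uses data already scheduled and costs only wording.

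If the team wants to keep the PCL-5 open as an outcome for the definitive trial, the alternative is to give it to all participants at baseline, 6 weeks and 3 months, with the PC-PTSD-5 kept as a screen. That removes one branching rule in REDCap and adds 20 self-report items per survey for screen-negative participants, or up to 3 × 20 = 60 items for someone negative throughout. In a trial that is itself testing retention and acceptability, that burden is a real trade-off. This choice has to be made before data collection, because the missing scores cannot be obtained afterwards.
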